### Sample size calculation

The sample size for this study was estimated using the following parameters: F-test, mixed between-within subjects analysis of variance (ANOVA); alpha (*α*) level of 0.05 (5% chance of drawing a false positive conclusion or committing type I error); power of 0.80 (80% probability of avoiding false negative conclusion; effect size of 0.20 (small effect size was used as no similar RCT could be found); and correlation among repeated measures of 0.5. Based on these assumptions, the total sample size required is 42. However, while accounting for 15% (*n* = 6) dropout rate, a minimum sample size of 48 participants (24 per group) will be finally required. The sample size calculation was performed with G-Power software version 3.1.9.2 for Windows [58]. 

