### Statistical analysis

Descriptive statistics of mean, standard deviation, percentage and frequency will be used to summarise the data. Comparison of baseline categorical variables among groups will be conducted using Fisher’s exact test or chi-square test and for continuous variables using independent *t*-test or Mann–Whitney *U* test where applicable. Intention-to-treat principle will be used for the primary statistical analysis by including each participant’s available data in accordance with original allocation and irrespective of the level of attendance. The primary and secondary outcomes will be analysed using linear mixed-effects models (LMMs) by including time (4, 8 and 20 weeks, baseline will be the reference), treatment (overground walking with paretic lower limb loading and overground walking without paretic lower limb loading) and a time × treatment interaction as fixed effects, and a random intercept to account for within-subject correlations. Treatment effect will be defined as the adjusted between-group difference and the associated 95% confidence intervals (CI). We opted to use LMMs because it provides unbiased estimates when data are missing at random [59]. Additionally, per-protocol analysis using the LMMs will be performed as sensitivity analysis by excluding randomised participants who did not received allocated intervention, or who attended fewer than 18 treatment sessions, received proscribed concomitant intervention known to influence gait, and experienced exclusionary medical conditions listed in the study exclusion criteria. All the statistical procedures will be performed using SPSS version 23.0 (IBM Co., Armonk, NY, USA) at a probability level of 0.05.

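### The sample size section claims 80% power for a small effect, but the f = 0.20 behind its total of 42 corresponds to a between-group difference of about 0.85 to 0.92 SD

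*Protocol article*

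**What the plan says.** The Sample size calculation section of the protocol article bases the trial on an "F-test, mixed between-within subjects analysis of variance (ANOVA", with alpha 0.05, "power of 0.80 (80% probability of avoiding false negative conclusion", "correlation among repeated measures of 0.5" and an "effect size of 0.20 (small effect size was used as no similar RCT could be found". From these inputs "the total sample size required is 42", and after allowing for 15% dropout "a minimum sample size of 48 participants (24 per group) will be finally required". The section does not say which ANOVA effect was powered (between, within or interaction) or how many measurements were entered. It gives no standard deviation and no target difference in cm or m/s.

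The Statistical analysis section then specifies a linear mixed model with time (baseline as reference), treatment, their interaction and a random intercept. It states: "Treatment effect will be defined as the adjusted between-group difference and the associated 95% confidence intervals (CI". It names no visit for this difference and gives no power for it. The outcomes section plans four assessments: baseline and weeks 4, 8 and 20.

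**The concern.** A reader will take the sample size section to mean that the trial can detect a small difference between the arms with 80% probability. The effect size is on the scale of a repeated-measures F-test, where 0.20 measures how much the between-group difference varies across visits. It is not a between-group difference of 0.20 SD, nor necessarily one of 0.40 SD. If the f = 0.20 that gives 42 is really a large difference, the stated sensitivity is misleading.

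What is at stake is how a non-significant result is read. The two arms receive the same programme apart from the sandbag, and the protocol commits to publishing negative or inconclusive results. A null result set beside the present wording could be taken as strong evidence against a small benefit, which a trial of this size cannot provide.

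**Working it through.** **Inputs.** From the protocol: effect size 0.20, alpha 0.05, power 0.80, correlation ρ = 0.5, 42 evaluable (21 per arm), 48 randomised, four planned assessments. Assumed: 0.20 is Cohen's f, as F-tests in the named software use; sphericity holds; the outcome SD is constant over visits and set to 1; the between-group contrast is tested two-sided at 0.05.

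**Step 1: reproduce the 42.** With N participants, m measurements and two groups:
- Interaction or within-subject test: λ = f²Nm/(1 − ρ), with (m − 1) and (N − 2)(m − 1) degrees of freedom.
- Between-group test: λ = f²Nm/(1 + (m − 1)ρ), with 1 and N − 2 degrees of freedom.

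| Test | m | N for 80% | Power at N = 42 |
|---|---|---|---|
| Interaction or within | 3 | 42 | 0.803 (λ = 0.04×42×3/0.5 = 10.08) |
| Interaction or within | 4 | 36 | 0.871 (λ = 0.04×42×4/0.5 = 13.44) |
| Between groups | 3 | 134 | 0.341 (λ = 5.04/2 = 2.52) |
| Between groups | 4 | 126 | 0.360 (λ = 6.72/2.5 = 2.69) |

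The stated total therefore comes from the within-subject or interaction test with 3 measurements. With 4 measurements, 42 appears only under inputs that the section does not give (a non-sphericity correction of 0.8, or alpha 0.025).

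**Step 2: what f = 0.20 means on that test.** Let D be the between-group difference at each visit in SD units. For two equal groups, the interaction f is half the population SD of D across visits. Baseline is measured before randomisation, so its true difference is zero. If the benefit is a constant d afterwards:
- 3 measurements, pattern (0, d, d): SD = d√(2/9) = 0.4714d, so f = 0.2357d and d = 0.20/0.2357 = 0.85.
- 4 measurements, pattern (0, d, d, d): SD = d√(3/16) = 0.4330d, so f = 0.2165d and d = 0.20/0.2165 = 0.92.

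**Step 3: the between-group difference in the planned analysis.** With n = 21 per arm, the standard error is s√(2/21) = 0.3086s, where s depends on the contrast. The results use the noncentral t. As a check for the first row, the normal approximation gives (1.960 + 0.842) × 0.3086 = 0.865.

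| Contrast | s at ρ = 0.5 | Difference for 80% power | Power at 0.40 SD |
|---|---|---|---|
| Single-visit change | √(2(1 − ρ)) = 1.000 | 0.87 (120 df) to 0.89 (40 df) | 24–25% |
| Single visit, baseline-adjusted | √(1 − ρ²) = 0.866 | 0.77 | 31% |
| Mean of three post-baseline visits minus baseline | √((1 − ρ)(4/3)) = 0.816 | 0.71 to 0.72 | 34–35% |
| Mean of three post-baseline visits, baseline-adjusted | √((1 + 2ρ)/3 − ρ²) = 0.645 | 0.57 | 50% |

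The 0.40 SD column is an assumption. It converts f = 0.20 by the two-group rule d = 2f and appears nowhere in the protocol.

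**Step 4: sensitivity.** If all 24 per arm are analysed, the single-visit change figure is 0.81 to 0.83 SD, and 0.72 SD with baseline adjustment. With 21 per arm and assumed correlations of 0.7, 0.8 and 0.9, single-visit change needs about 0.68, 0.55 and 0.39 SD.

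**The case against.** The strongest reply is that the sizing calculation and the planned analysis agree better than they seem to. The mixed model contains the time-by-treatment interaction with a random intercept, which is close to the interaction test that reproduces 42. At the effect used for sizing, 0.85 to 0.92 SD constant after baseline, the single-visit change contrast has about 77% to 84% power. This stands: the 80% roughly carries over to the between-group difference.

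A reader might therefore go too far in three ways. One is to infer that the trial has only about 25% power for the effect it was sized on; that figure belongs to 0.40 SD, which is not a protocol figure. Another is to infer that 126 to 134 participants are needed. Those numbers belong to the between-group main effect averaged over all visits including baseline, and nothing in the analysis section makes that the deciding test. The third is to take 0.87 SD as the single answer. The protocol does not define the visit or the form of adjustment, and other reasonable contrasts or a higher correlation detect smaller differences.

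It can also be said that the plan already reports 95% confidence intervals and foresees inconclusive results. That limits the harm but does not correct the label. At the protocol's own correlation of 0.5, no contrast checked gives 80% power at 0.40 SD, let alone below it.

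**Conclusion.** The concern holds as a mislabelled effect size and power. It is not a slip in arithmetic, since 42 is reproducible. The sample size section is wrong as written in presenting 80% power for a small effect: on the test that yields 42, f = 0.20 is a large between-group difference. For the treatment effect defined in the analysis section, the difference detectable with 80% power at ρ = 0.5 and 21 per arm lies between about 0.57 and 0.89 SD, depending on the contrast.

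These figures rest on reading 0.20 as Cohen's f, on equal variances and correlations across visits, and on no true baseline difference. The 0.85 and 0.92 SD conversions also need a benefit that is constant after baseline. Because the number of measurements entered is not stated, that 3 were used is inferred from the total.

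**What to change.** Keep 48 randomised and reword the sample size section:
- Name the ANOVA effect and the number of measurements entered, and reconcile that number with the four planned assessments.
- Delete the description of the effect size as small.
- State the between-group difference detectable with 80% power for the mixed-model analysis, with the contrast and correlation assumed. For example: with 42 analysed, correlation 0.5 and two-sided 0.05, about 0.87 to 0.89 SD for change at one visit, or about 0.77 SD if baseline-adjusted.
- Express that difference in cm for step length and m/s for gait speed, using SDs from pooled, blinded baseline data. SDs from the 18-person pilot can serve only if the pilot measured gait. The protocol reports from it only the tolerability of the weight and the absence of adverse events.
- Add that a non-significant result will be interpreted from the 95% confidence interval and not as evidence of no benefit.

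The cost is a text amendment and a simple blinded summary of baseline SDs, with no extra participants and no change to the analysis model. The downside is a less favourable stated sensitivity.

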### Statistical analysis

Descriptive statistics of mean, standard deviation, percentage and frequency will be used to summarise the data. Comparison of baseline categorical variables among groups will be conducted using Fisher’s exact test or chi-square test and for continuous variables using independent *t*-test or Mann–Whitney *U* test where applicable. Intention-to-treat principle will be used for the primary statistical analysis by including each participant’s available data in accordance with original allocation and irrespective of the level of attendance. The primary and secondary outcomes will be analysed using linear mixed-effects models (LMMs) by including time (4, 8 and 20 weeks, baseline will be the reference), treatment (overground walking with paretic lower limb loading and overground walking without paretic lower limb loading) and a time × treatment interaction as fixed effects, and a random intercept to account for within-subject correlations. Treatment effect will be defined as the adjusted between-group difference and the associated 95% confidence intervals (CI). We opted to use LMMs because it provides unbiased estimates when data are missing at random [59]. Additionally, per-protocol analysis using the LMMs will be performed as sensitivity analysis by excluding randomised participants who did not received allocated intervention, or who attended fewer than 18 treatment sessions, received proscribed concomitant intervention known to influence gait, and experienced exclusionary medical conditions listed in the study exclusion criteria. All the statistical procedures will be performed using SPSS version 23.0 (IBM Co., Armonk, NY, USA) at a probability level of 0.05.

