### Participants’ recruitment

The study participants will be drawn from a population of patients with stroke referred for outpatient physiotherapy at MMSH and MAWTH in Kano State. They will be given all the necessary information about the procedures and potential benefits of the study. Written informed consent will be obtained from all the participants after assessment for eligibility. To be eligible for the study, patients must meet the following criteria: (1) unilateral ischemic or hemorrhagic stroke occurring at least 3 months before enrolment; (2) male or female between the age of 20 and 70 years; (3) Having Modified Rankin Scale (MRS) scores of 1, 2 or 3 and also able to walk at least 10 m independently without assistive device; and (4) ability to follow verbal instructions. Patients with one or more of the following criteria will be excluded from the study: (1) cognitive impairments; (2) visual impairments; (3) musculoskeletal disorders that may affect gait such as arthritis; (4) other neurological disorders such as Parkinson's disease, multiple sclerosis; (5) cardio-respiratory conditions that may limit participation such as atelectasis; and (6) concurrent participation in other interventional clinical trials.

Demographic and clinical characteristics such as age, gender, marital status, education level, occupational level, duration of stroke, laterality, leg dominance, blood pressure, weight, height, body mass index (BMI), side of affectation and MRS scores will be obtained using a prepared study proforma. Assessment of baseline outcome variables will be then conducted prior to randomisation. A specific ID will be given to all participants for recognition.

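### The treatment effect is called adjusted, but the stated model names no covariate, contrast or visit and leaves baseline means free by arm; at the plan's correlation of 0.5 this costs about a quarter of the information per visit

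*Protocol article*

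**What the plan says.** The Statistical analysis section applies linear mixed-effects models to all primary and secondary outcomes, "by including time (4, 8 and 20 weeks, baseline will be the reference"), with treatment and a time × treatment interaction as the other fixed effects and a random intercept per participant. The next sentence reads: "Treatment effect will be defined as the adjusted between-group difference and the associated 95% confidence intervals (CI"). It does not say what the difference is adjusted for, at which visit it is taken, or which model term it is. The baseline value, the Modified Rankin stratum used in randomisation and the centre are all absent from the listed terms.

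On timing, the Participants' recruitment section states: "Assessment of baseline outcome variables will be then conducted prior to randomisation". The Randomisation and blinding and Outcome assessments sections agree. The Sample size calculation assumes a "correlation among repeated measures of 0.5".

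**The concern.** Baseline is a level of the time factor, so it enters the model as an outcome. Treatment also has its own main effect, so the two arms' baseline means are estimated separately. Because baseline precedes randomisation, the expected baseline difference is zero, and the model spends information estimating a quantity that the design already fixes.

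The effect can also be read in two ways:

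- **Interaction contrast.** The time × treatment coefficient at a visit, which is the between-arm difference in change from baseline.
- **Visit-mean contrast.** The between-arm difference in model means at a visit. With complete data this is the raw difference at that visit.

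Within one trial the two estimates differ by the observed baseline gap. With 21 per arm that gap has a standard deviation of √(2/21) = 0.31 outcome SDs by chance alone. For a primary analysis in a trial of 48, this choice should not be left open until the data are seen. Both readings also forgo precision that the baseline measurement would supply.

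**Working it through.** **Inputs, all from Sample size calculation unless noted**

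- "F-test, mixed between-within subjects analysis of variance (ANOVA"), "alpha (*α*) level of 0.05", power 0.80.
- "effect size of 0.20 (small effect size was used as no similar RCT could be found"), read here as Cohen's f because the test is an F-test.
- Correlation ρ = 0.5 among repeated measures.
- "the total sample size required is 42", that is 21 per arm before the dropout allowance.
- Four assessments: baseline and weeks 4, 8 and 20 (Outcome assessments and follow-ups).

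**Step 1: the plan's own figure.** For the within-between interaction, λ = N f² m/(1 − ρ), with m − 1 and (N − 2)(m − 1) degrees of freedom. The number of measurements m is not stated.

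- m = 3: λ = 42 × 0.04 × 3/0.5 = 10.08, power 0.803. This reproduces 42.
- m = 4, the number of visits planned: λ = 42 × 0.04 × 4/0.5 = 13.44, power 0.871.

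**Step 2: variance of a single-visit contrast.** Assume equal variances σ², a common correlation ρ (which a random intercept implies), complete data and n per arm. In units of 2σ²/n:

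- interaction (change) contrast: 2(1 − ρ)
- visit-mean contrast: 1
- baseline-adjusted contrast, by covariate or by a common baseline mean: 1 − ρ²

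The change contrast subtracts the whole baseline gap, the visit-mean contrast subtracts none of it, and the adjusted contrast subtracts ρ times the gap. At ρ = 0.5 the first two are equally far from the best weight, so they lose the same amount.

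| ρ | Interaction | Visit mean | Adjusted | Loss, interaction: (1 − ρ)/2 | Loss, visit mean: ρ² |
|---|---|---|---|---|---|
| 0.3 | 1.40 | 1.00 | 0.91 | 35% | 9% |
| 0.5 | 1.00 | 1.00 | 0.75 | 25% | 25% |
| 0.7 | 0.60 | 1.00 | 0.51 | 15% | 49% |
| 0.9 | 0.20 | 1.00 | 0.19 | 5% | 81% |

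**Step 3: the same from the full four-visit model.** Generalised least squares with σ = 1, ρ = 0.5 and 21 per arm gives a variance of 2/21 = 0.0952 for either reading under the stated model. With a common baseline mean it gives 0.0714. The ratio is 0.75.

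**Step 4: finite-sample check.** Estimating the baseline slope costs a factor of about 1 + 1/(N − 4), so 0.75 × (1 + 1/38) = 0.770. A simulation of 20,000 trials at 21 per arm gave variances of 0.0946 (change), 0.0953 (visit mean) and 0.0729 (baseline as covariate). The ratio to the change contrast is 0.77, a 23% loss.

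**Step 5: what this means.**

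- Interval width: 1/√0.75 = 1.155 and 1/√0.77 = 1.140, so the interval is 14–15% wider than needed.
- Participants: 42/0.75 = 56 under the stated model would match 42 with adjustment (about 55 using 0.77).
- Power: a single-visit comparison with 80% power under the stated model would have about 90% with adjustment (large-sample ratio of 0.75).

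**The case against.** Time, treatment and their interaction with a random intercept is a standard longitudinal analysis and is valid under randomisation. A reader might infer from this point that the result would be biased. It would not be; the loss is of precision and of definition only.

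A reader might also infer that the model adjusts for nothing. That goes too far. With baseline as the reference level, each interaction coefficient subtracts baseline, and this coding makes the interaction the more natural reading. The section does not say so, however, and subtraction is not the efficient use of baseline. Nor does the visit-mean reading ignore baseline altogether once visits are missing, because the random intercept then carries some of its information. The complete-data figures above are a simplification in that respect.

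The power target does not depend on the proposed gain. On the plan's own assumptions, the interaction F-test at 42 has power 0.803 with three measurements or 0.871 with four. The documents therefore do not support the inference that the missing adjustment leaves the trial underpowered by its own calculation.

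Finally, this is a condensed article, and a fuller plan might say what adjusted means. That has some force for the single word. It has less for the model, whose fixed effects are listed as though complete.

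**Conclusion.** The point holds as a matter of precision and definition. The term *adjusted* has no covariate behind it in the stated model, the contrast and visit are not fixed, and the arms' baseline means are free without need. At ρ = 0.5, a single-visit effect loses 25% of the information in large samples and about 23% at 21 per arm, on either reading.

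The size rests on the assumed correlation, for which the plan gives no source, and on compound symmetry with complete data. A quarter is not a ceiling: other correlations give the losses tabulated above, and an effect averaged over the three follow-up visits at ρ = 0.5 would lose 37.5% (variance 0.0635 against 0.0397).

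It is tempting to take the test–retest value of 0.94–0.99 for gait speed in Table 2 as evidence that the loss is at one extreme. Those figures describe measurement reliability, not the correlation between baseline and a visit weeks later under training, so they do not settle it. If that correlation did prove high, the interaction would lose little and the visit-mean contrast most of its information, which is when leaving the choice open costs most.

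**What to change.** Replace the model statement with one of these:

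1. Model weeks 4, 8 and 20 as outcomes, with visit, treatment, treatment × visit, the baseline value and baseline × visit as fixed effects.
2. Keep all four visits as outcomes and constrain the arms to one common baseline mean by including treatment terms only for the post-baseline visits.

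For the second option, code three indicators, each equal to 1 for loading-arm records at week 4, 8 or 20 and 0 otherwise, and enter them alongside time. Deleting the treatment main effect while keeping the full time × treatment factor does not impose the constraint; it only reparameterises the same model.

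Then state that the treatment effect is the adjusted between-group difference, with its 95% confidence interval, at a named visit from that model.

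No new data or visits are needed. The second option keeps everyone with a baseline measurement, in line with the plan's available-data intention-to-treat rule. The cost is the revised wording and, under Trial status and amendments, notice to the ethics committee and an update of the registry entry. The change should be made before allocation is linked to outcome data.

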### Data management

All participants will be recognised only by their ID codes. Data will be stored in secured manner using paper files and in computer hard drive using Microsoft Excel. Participants’ information will be kept strictly confidential and will be accessed only by members of the trial team or ethics committee. Only anonymised data will be made available to other researchers to enable international prospective analyses. All data values will be double-checked by the outcome assessors for errors and missing values before analysis.

### Data monitoring

The study will not have a formal data monitoring committee since the study involves a low-risk intervention. Instead, the authors of this study protocol (identical to trial management committee) will be responsible for monitoring patients’ recruitment, treatment and attrition rates, as well as any other concerns related to the study every 2 weeks.

